### 2.7. Sample Size Estimation

Power calculation was performed using G*Power software [48] (University of Duesseldorf, Germany) with a two-tailed alpha of 0.05, a beta of 90%, and an estimated effect size of Cohen’s d = 0.55. This resulted in a necessary sample (as treated AT) of at least 52 members per group at posttest. 

As the dropout rate is difficult to foresee in the current political and economic situation, we assumed a drop-out rate of 35% per intervention cycle. Thus, we need to enroll 80 participants in the IG and the CG, respectively. Hence, at least 160 adolescents need to be included in the study, distributed across the six climbing groups (each consisting of 12–14 participants) and the control group. Including the waitlist-control group (which will be offered the intervention after the study period), up to a total of 160 adolescents should thus be provided with a climbing program. Figure 2 gives an estimated overview about sample sizes.

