#### 2.9.2. Secondary Outcome Measure

Psychological distress is measured with the Arabic version of the K-6 Distress Scale [49,50]. The K-6 consists of six items covering the main depressive symptoms (i.e., hopelessness, feeling worthless, nervous, so sad that nothing can cheer me up, and the feeling that everything is an effort). Sum scores range from 6 to 30 with higher scores signifying higher psychological distress. The authors of the Arabic validation study used 16.25 as the cut-off score for psychological disorders.

Self-efficacy is measured with the Arabic version of the general self-efficacy scale (GSE) [51]. The GSE measures optimistic self-beliefs about coping with a variety of difficult demands in life. Its 10 items can be rated on a 4-point scale ranging from 1 (not at all true) to four (exactly true). The total score ranges from 10 to 40 with higher scores indicating higher self-efficacy. The GSE has good psychometric properties [52].

Social cohesion is measured with a five-item set and an additional single-item measure from the ARK Regular Perception Survey. This survey is used specifically to analyze social tension throughout Lebanon. The items were modified to fit the situation experienced by adolescents. The five-item set uses a 5-point Likert scale ranging from 1 (very disagreeable) to 5 (very agreeable) to ask how agreeable five different scenarios are. The questions always refer to members of the other nationality, and the scenarios involve playing with or attending school with children of the other nationality, living next door to or sharing a workplace with a member of the other nationality, or having a family member who marries someone of the other nationality. In the additional single-item measure, participants are asked to rate how much they agree with the phrase: “Lebanese and Syrians share many values and have compatible lifestyles” on a 4-point Likert scale ranging from 1 (strongly agree) to 4 (strongly disagree) [5]. 

The following variables are recorded as possible variables of influence or confounding variables in the questionnaire format:Sociodemographic data: sex, age, school enrollment, nationality, living conditionsPhysical activityMedical conditionsClimbing experience

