### 2.11. Data Analysis

#### 2.11.1. Quantitative Data

The data analyses will be performed with the “IBM SPSS Statistics 28” software. To assess the quality of the group allocation, the baseline data from the intervention and control groups will be examined for statistically significant differences. All data will be investigated for plausibility. Participants who drop out of the study but are still available for the posttest will be interviewed subsequently. A missing data evaluation will be carried out, and missing values will be imputed with EM-Imputation [54]. The primary data analytic strategy will be “per protocol”. As a sensitivity analysis, an additional analysis with “intention to treat” will be performed. The level of statistical significance will be set at *p* ≤ 0.05. Mixed ANOVAs (time × group) will be used to determine differences between the groups. Additionally, regression analyses will be used to test the hypotheses and check for possible confounders. Differences between groups will be determined before analysis, and if there are significant differences in important sociodemographic variables, appropriate statistical methods (e.g., propensity score matching) will be used. Secondary outcomes will be tested in an exploratory fashion with *t* tests for independent samples.

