The strengths of the study are the large sample size, the existence of a control group, the mixed-methods approach, the use of manualized treatment options, the naturalistic setting, and therefore, the pragmatic nature of the evaluation of a real-world program. One limitation is the lack of randomization. In this specific study, randomization may also have been a limitation because it may have resulted in the exclusion of female participants for cultural reasons. Being female in a refugee context is a risk factor for mental distress, especially depression [38]. Syrian refugees in Lebanon often live according to religious or cultural traditions with a strong desire to protect girls from potential harmful encounters outside the family. To include female participants, we decided not to randomize the group to allow family members who also need to comply with the inclusion criteria (e.g., mostly brothers, sisters, cousins) to participate together in the same intervention group. In addition, we offered female-only groups, and ClimbAID staff travel on the buses that collect all the participants from their homes. No participants must use public transportation. We therefore concluded that the disadvantages of randomization (which would prevent a vulnerable group from participating in the intervention) outweighed the positives. If the groups differ at baseline in relevant factors, appropriate statistical methods (e.g., propensity score matching) will be applied.

Another potential limitation is that the bouldering intervention cannot be blinded with respect to facilitators or participants. All outcome measures are self-assessed and, therefore, are also not blinded. Third, in the absence of exclusion criteria regarding possible diagnoses or levels of psychological distress, it is possible that we will obtain a heterogeneous sample, with the associated advantages of a naturalistic design and low-threshold intervention and the disadvantages of potentially diluted intervention effects.

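### Confounder control beyond an undefined regression check depends on significant baseline differences, a weak trigger for a partly self-selected comparison, and the method is chosen afterwards

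*Protocol article*

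**What the plan says.** Section 2.11.1 makes two linked statements. First, "the baseline data from the intervention and control groups will be examined for statistically significant differences". Second, "if there are significant differences in important sociodemographic variables, appropriate statistical methods (e.g., propensity score matching) will be used". The only significance level given there is 0.05.

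The Discussion returns to the step as the answer to incomplete randomisation, with another trigger: "If the groups differ at baseline in relevant factors, appropriate statistical methods (e.g., propensity score matching) will be applied". Significance is not mentioned, and the restriction to sociodemographic variables is gone.

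Two other parts of section 2.11.1 bear on the point. The main between-group analysis is a time × group mixed ANOVA, which uses baseline WEMWBS but no other covariate. Regression analyses are added, without any condition, to test the hypotheses and look for confounders; no covariates are named.

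Section 2.9.2 introduces its covariate list with "The following variables are recorded as possible variables of influence or confounding variables". The list has five sociodemographic items (sex, age, school enrolment, nationality, living conditions) and, as separate items, physical activity, medical conditions and climbing experience.

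Under section 2.6, about 20% of eligible applicants select their own timing, and hence their arm. Family and women-only needs are accommodated, and the remaining applicants are allocated at random.

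**The concern.** A baseline p-value reflects sample size as much as imbalance, and says nothing about how strongly the variable predicts WEMWBS. A strong predictor with a moderate, non-significant imbalance stays out of the step. A weak predictor that differs by chance sets it off.

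Read literally, the section 2.11.1 trigger covers sociodemographic variables only. Physical activity, medical conditions and climbing experience could then never set it off, although section 2.9.2 lists them as possible confounders. In a climbing trial, the first and last are obvious candidates to differ between people who want to start now and people who wait.

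The remedy is also open. Which method follows is decided once the baseline differences are known, so the analysis behind the main conclusion depends on the data. At stake are residual confounding in the WEMWBS comparison and, with some choices of method, part of the sample.

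**Working it through.** **Inputs from section 2.7.** The calculation uses d = 0.55 "with a two-tailed alpha of 0.05, a beta of 90" per cent, which I read as power. It arrives at "at least 52 members per group at posttest". Then "we assumed a drop-out rate of 35% per intervention cycle", so "we need to enroll 80 participants in the IG and the CG, respectively".

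**The plan's own figures.** The formula is n per arm = 2(z₀.₉₇₅ + z_power)² / d².
- 80% power: 2(1.960 + 0.842)² / 0.3025 = 51.9, so 52.
- 90% power: 2(1.960 + 1.282)² / 0.3025 = 69.5, so 70.
- Dropout: 52 / 0.65 = 80, as stated.

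The 52 therefore fits 80% power, not 90%. That is a separate matter. Here 52 (completers) and 80 (enrolled) serve only as the two sizes at which a baseline test might be run, since the article does not say which set is tested.

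**Chance that the test misses a true imbalance.** For a standardised difference δ the noncentrality is δ√(n/2), and the miss rate is approximately 1 − Φ(δ√(n/2) − 1.960). Example: δ = 0.3, n = 52 gives 0.3 × √26 = 1.530, and 1 − Φ(−0.430) = 0.67. Values from the noncentral t:

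| True imbalance | 52 per arm | 80 per arm |
|---|---|---|
| 0.2 SD | 83% | 76% |
| 0.3 SD | 67% | 53% |
| 0.4 SD | 48% | 29% |
| 0.5 SD | 29% | 12% |

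The smallest observed difference that reaches p ≤ 0.05 is t₀.₉₇₅ × √(2/n): 0.39 SD at 52 per arm and 0.31 SD at 80.

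**Bias that can pass unnoticed.** For one covariate this is roughly (observed imbalance) × (correlation with the analysed outcome). With an assumed correlation of 0.5, the limit is 0.39 × 0.5 = 0.19 SD at 52 per arm, which is 35% of the planned 0.55. With 0.3 it is 0.39 × 0.3 = 0.12 SD, or 21%.

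**False triggers.** If k independent covariates are balanced in truth, at least one is significant with probability 1 − 0.95^k: 23% for k = 5 and 34% for k = 8.

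**Type I error.** I simulated one confounder correlated 0.5 with the outcome, no treatment effect, and adjustment by regression only when the baseline test is significant. With true imbalances of 0.2 to 0.4 SD, the rejection rate was 5.3% to 6.0% at 52 per arm and 5.4% to 5.7% at 80. Always adjusting gave 4.9% to 5.1%.

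**Sample lost if matching follows.** No ratio or caliper is given, so everything here is assumed: 1:1 greedy matching without replacement, six normal covariates, equal arms, and only datasets with at least one significant baseline test.
- Caliper 0.2 SD of the logit: 31% to 42% dropped at 52 per arm, 25% to 38% at 80.
- Calipers from 0.1 to 0.5 SD: 24% to 47% at 52 per arm, 20% to 42% at 80.
- No caliper: none dropped. Regression and weighting also drop nobody.

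If a third of 52 were lost, 35 per arm would remain, and power at d = 0.55 would be 62% against 79% (t test).

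**The case against.** Four stronger readings are tempting, and the article does not support them.

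- *That confounders are handled only after a significant test.* Section 2.11.1 plans regression for confounders unconditionally, the mixed ANOVA takes in baseline WEMWBS, and the Discussion does not require significance. What stands is that the regression names no covariates, is an addition to the mixed ANOVA, and is not said to govern the primary result if the two disagree.
- *That the plan will match, lose a third of its sample and see power collapse.* Matching is an example in both places. The loss runs from 0% to 47% depending on choices the article does not make.
- *That most relevant imbalances are missed.* This is true at 0.2 and 0.3 SD, about even at 0.4 SD with 52 per arm, and false at 0.5 SD. The article defines no relevant size.
- *That the error is large.* For a single confounder it is not.

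The best argument on the other side concerns allocation. If only 20% self-select and the rest are random, an overall imbalance of 0.3 SD needs 0.3 / 0.20 = 1.5 SD among the self-selectors, and 0.2 SD needs 1.0 SD. That would be a strong contrast. It stands as a reason to call the imbalances assumed. It is weakened by the accommodation of family groups, by the Discussion's statement that the group was not randomised, and by a per-protocol primary analysis with 35% expected dropout, which can unbalance even those allocated at random.

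A full covariate list may fairly be left to an analysis plan that is not shown. A trigger based on significance is different, because the article states it as the rule.

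**Conclusion.** The point holds as one about the stated rule. Outside a regression check whose role is undefined, further confounder control waits on significant differences in sociodemographic variables. The Discussion gives a trigger that does not agree, and the method is chosen after the differences are seen.

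For imbalances of 0.2 to 0.3 SD the rule fails to act in 67% to 83% of cases at 52 per arm and 53% to 76% at 80. Taken literally, it passes over three of the eight recorded possible confounders. Its effect on type I error is modest, about 6% for one confounder.

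The miss rates follow from the planned sample sizes once an imbalance is assumed. The bias, the type I error and the matching losses rest on assumed correlations, imbalances and matching settings. The change is worth making because the better rule uses data that are already collected.

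**What to change.** Remove the significance trigger from section 2.11.1 and bring the Discussion into line. Adjust the primary WEMWBS model in every case for a short list fixed in advance: t0 WEMWBS, age, sex, nationality, school enrolment, physical activity, climbing experience, and self-selected versus random allocation. The last is not in the section 2.9.2 list but is known from the allocation process. State that this model gives the primary result.

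Describe baseline with standardised differences instead of p-values. Keep any propensity method as a sensitivity analysis, preferably weighting that retains all participants.

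The cost is wording and a few degrees of freedom. With two terms for nationality and one for each other item, the list uses 9 parameters against 2 × 52 = 104 participants at posttest. No new data collection is needed.

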#### 2.2.3. Study Design and Setting

The research is designed as a waitlist-controlled trial, with the implementation of a manualized climbing intervention for Lebanese adolescents and adolescent refugees living in the Bekaa region of Lebanon. The plan is for the CG not to receive any study-specific intervention while the IG receives the intervention, but the CG members will be invited to participate in an upcoming cycle of the climbing program. Members of the CG will, therefore, be offered the same intervention as the IG after their waiting period. For the individual participant, the study duration will be up to approximately 12 weeks with 8 weeks of intervention (see Figure 1), followed by the voluntary participation of the CG members in the intervention. The procedure involves administering surveys to both groups (IG and CG) before the intervention begins (t0, pretest) and immediately after the intervention ends (t1, posttest). During the second half of the intervention period, qualitative semi-structured interviews will be conducted with members of the IG focusing on modes of action and outcomes of the intervention. The participant timeline is presented in Figure 1. Trial Registration Data are presented in Table 1 (ISRCTN13005983, registered April 2022, registered prospectively).

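### Baseline scores are collected on every scale, but the planned t tests and time × group ANOVA do not adjust for them, in a design where arms may differ at baseline

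*Protocol article*

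**What the plan says.** Section 2.2.3 has both arms complete the surveys "before the intervention begins (t0, pretest) and immediately after the intervention ends (t1, posttest"), so each outcome has a baseline score (t0) and a posttest score (t1).

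Section 2.11.1 then names the methods:

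- Group differences: "Mixed ANOVAs (time × group) will be used to determine differences between the groups". Regression analyses are added to test the hypotheses and look for confounders, with no covariates named.
- Distress (K-6), self-efficacy (GSE) and social cohesion: "Secondary outcomes will be tested in an exploratory fashion with *t* tests for independent samples". Whether the t1 score or the change score is tested is not stated.
- Imbalance: baseline data are tested for significant differences between arms. Methods such as propensity score matching follow if sociodemographic characteristics judged important differ significantly. The Discussion (section 3) words the trigger more broadly, as any relevant baseline factor, but it stays conditional.

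Section 2.6 lets about 20% of eligible applicants, those available for only one cycle, choose their timing and so their arm. It also makes room for family members who must attend together and for women-only groups. The Discussion names the absence of randomisation as a limitation. Nowhere is an outcome's own t0 score named as a covariate.

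**The concern.** Two things are at stake.

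The first is bias. Where some participants choose their arm, the arms may start at different levels of distress, self-efficacy or social cohesion. A t test on t1 scores carries part of such a gap into the estimated effect. A change score subtracts the gap but over-corrects whenever r is below 1, leaving a regression-to-the-mean remainder of opposite sign. The safeguard in section 2.11.1 responds to sociodemographic differences, not to baseline outcome scores, and only when they reach significance.

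The second is precision. A linear model of t1 on arm plus t0 (ANCOVA) uses information that the trial already collects. Under the usual equal-variance assumptions it is never less precise than either planned test, apart from one degree of freedom and a small loss if the arms differ at baseline.

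**Working it through.** **Inputs from section 2.7.** Testing is "with a two-tailed alpha of 0.05", with "an estimated effect size of Cohen’s d = 0.55" and "at least 52 members per group at posttest". The stated 90% is written as beta and read here as power. For attrition, "we assumed a drop-out rate of 35% per intervention cycle" and "we need to enroll 80 participants in the IG and the CG, respectively".

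**Inputs that are assumed.** The documents give no baseline–posttest correlation r, so 0.3 to 0.8 is shown. They do not say which SD standardises d; the t1 SD is assumed, with equal SDs at t0 and t1.

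**Step 1: the plan's own figure.** n per arm = 2(z₀.₉₇₅ + z_power)²/d².

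- 90% power: 2(1.960 + 1.282)²/0.3025 = 69.5, so 70 (71 with the t distribution).
- 80% power: 2(1.960 + 0.842)²/0.3025 = 51.9, so 52 (53 with t).
- Attrition: 52/0.65 = 80, which agrees with the plan.

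The 52 therefore matches 80% power, not 90%; the exact t-test power at 52 per arm is 79.3%. That is a separate matter. Here 52 is simply the planned number analysed.

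**Step 2: variance factors, relative to a t1 comparison.**

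- t test on t1: 1
- change score (time × group with two time points): 2(1 − r)
- ANCOVA: 1 − r²

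ANCOVA is below the t1 factor by r², and below the change factor by 2(1 − r) − (1 − r²) = (1 − r)². Neither difference can be negative.

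**Step 3: power for WEMWBS.** Noncentrality = 0.55 × √(52/2)/√factor = 2.804/√factor, with 102 degrees of freedom (101 for ANCOVA).

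| assumed r | change | t1 only | ANCOVA | gain over t1 (points) | gain over change (points) |
|---|---|---|---|---|---|
| 0.3 | 65.1% | 79.3% | 82.9% | 3.6 | 17.8 |
| 0.4 | 71.8% | 79.3% | 85.8% | 6.5 | 14.0 |
| 0.5 | 79.3% | 79.3% | 89.4% | 10.1 | 10.1 |
| 0.6 | 87.4% | 79.3% | 93.5% | 14.1 | 6.1 |
| 0.7 | 94.8% | 79.3% | 97.3% | 18.0 | 2.5 |
| 0.8 | 99.2% | 79.3% | 99.6% | 20.3 | 0.4 |

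**Step 4: what a baseline gap leaves behind.** Let the intervention arm start b SD higher, and let the correct adjustment slope be r. The error is r·b in a t1 comparison and (r − 1)·b in a change-score contrast. For an illustrative b = 0.2:

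| assumed r | t1 comparison | change score |
|---|---|---|
| 0.3 | +0.06 SD | −0.14 SD |
| 0.5 | +0.10 SD | −0.10 SD |
| 0.7 | +0.14 SD | −0.06 SD |

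Against the only effect size in the protocol, 0.10/0.55 = 18% and 0.14/0.55 = 25%.

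**Step 5: would the baseline test flag such a gap?** With 80 per arm, the standard error of a baseline difference is √(2/80) = 0.158 SD, so significance needs about 1.975 × 0.158 = 0.31 SD. With 52 per arm it needs 1.983 × √(2/52) = 0.39 SD. An observed gap of 0.2 SD would pass unflagged even if the outcome scores were among the variables tested.

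**The case against.** **The primary test is not left with baseline imbalance.** A reader might infer that both planned analyses carry the baseline gap into the estimate. For time × group this is wrong: the gap is subtracted, and only the remainder (r − 1)·b stays. This objection stands.

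**ANCOVA is not automatically right here.** Where arms are partly self-selected, ANCOVA and change scores can target different effects, and neither is guaranteed unbiased. The mixed ANOVA is a defensible analysis, not an error. This also stands, and it is why both should be reported.

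**A loss of ten points is not a fact about this trial.** It holds for both tests only at r = 0.5. At r = 0.8 the primary test loses almost nothing. If d refers to the SD of change, which sections 2.2.1 and 2.7 do not rule out, the time × group power at 52 per arm is 79% whatever r is. Nor do the power figures transfer to the secondary outcomes: d = 0.55 belongs to WEMWBS, and no effect size is given for the others.

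**Safeguards exist and details may sit elsewhere.** Baseline data will be examined, regression is planned and propensity methods are available; a covariate list is commonly left to an analysis plan. It is also not stated that the arms will differ, only what happens if they do. All this is fair. But the t tests for secondary outcomes are a stated method, not an omitted detail, and the stated remedy is conditional on significance.

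**The secondary outcomes are exploratory.** That lowers the stakes, but their estimates will still be read as effects, and the adjustment uses data already in hand.

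**Conclusion.** The point holds in a limited form. The secondary outcomes are assigned a test that takes no account of the outcome's own baseline as a covariate, and the article does not say which score is tested. The primary comparison is a change-score test that may be weaker than the data allow. The imbalance safeguard does not reliably cover baseline outcome scores.

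The bias is conditional on a baseline gap: 0.06 to 0.14 SD in absolute size for a 0.2 SD gap over r = 0.3 to 0.7, with opposite signs for t1 and change-score analyses. The power gain applies to WEMWBS only, depends strongly on an r that the documents do not give, and assumes d in t1 SD units. The documents do not support a claim that the ANOVA is invalid, or that ANCOVA would remove all bias from self-selection. The change is worth making because the plan names the methods to be replaced and the cost is very small.

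**What to change.** 1. Replace the t tests for K-6, GSE and each social cohesion measure with a linear model of the t1 score on arm plus the matching t0 score. Fit it whatever the baseline significance tests show.
2. Prespecify the same model for t1 WEMWBS, and report the time × group ANOVA beside it so that any divergence in the self-selected part is visible. Say in advance which of the two carries the primary conclusion.
3. State the assumed r and the SD to which d = 0.55 refers.

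No further model terms are needed for this point. A fixed climbing-group term in particular would have no defined value in the control arm, because section 2.7 sets the six climbing groups apart from the control group.

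The cost is analysis wording and one further model per outcome. No data are added, which matters because Table 1 lists recruitment as complete. The change should be dated before outcomes are compared by arm. The one downside is that the two WEMWBS models may disagree, and that disagreement must then be reported.
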